### Randomization, allocation concealment, and blinding

An independent researcher who is not involved in recruitment, intervention delivery, outcome assessment, data management, or analysis will generate the 1:1 cluster allocation sequence after baseline data collection has been completed for all six participating homes. Because of the small number of clusters, covariate-constrained randomization will be used to reduce the risk of baseline imbalance on prespecified cluster-level characteristics: facility size (number of beds), dementia-care intensity (proportion of residents with dementia), staff-to-resident ratio, and aggregated baseline NPI-12 mean. The allocation algorithm will enumerate all possible 3-versus-3 cluster allocations, retain only those satisfying a predefined balance criterion on these characteristics, and draw one sequence at random from the retained set using R version 4.3 or later. The list of acceptable allocations and the chosen sequence will be archived and reported in the final trial publication. The allocation list will be held separately from site teams and released only to site coordinators after completion of baseline assessment. Baseline cluster descriptors will also be summarized before analysis to confirm balance and to document any residual imbalance for sensitivity analyses.

Because the intervention is visible in routine care, participants, direct caregivers, and staff delivering the intervention cannot be blinded. Outcome assessors will be registered nurses or research staff with prior experience in geriatric or dementia care, will not participate in intervention delivery, will be asked not to discuss group assignment with site staff, and will complete assessments in a location separate from intervention materials whenever possible. Before the trial starts, all assessors will complete a structured training program on the NPI-12 (including standardized vignettes and a reference manual) and the Barthel Index, and will demonstrate inter-rater agreement at an intraclass correlation coefficient of at least 0.75 on paired ratings of pilot vignettes; assessors who do not reach this threshold will receive additional training. Inter-rater agreement will be re-checked midway through the trial. Data files provided to the statistician will use masked group codes until the primary analysis syntax and analysis decisions have been finalized. Any accidental unblinding of assessors or statisticians will be documented, including the date, reason, and affected assessment or analysis stage.

### Intervention and comparator

The intervention is the staff-mediated doll-therapy care package plus routine nursing care. Each participant in the intervention arm will be offered an individual lifelike baby doll. The doll will be introduced as an optional comfort and activity object rather than as a real infant. Staff will avoid deceptive language that requires residents or families to accept a false belief, while also responding respectfully to residents’ spontaneous meanings and emotions. Before the intervention begins, staff will explain the purpose, potential benefits, and possible concerns to family caregivers or legally authorized representatives and will emphasize that participation is voluntary and may be paused or stopped at any time.

The estimand for this pilot trial is the effect of the doll-therapy care package as implemented in routine nursing-home care, comprising the individualized doll, staff training, structured introductory sessions, dignity-preserving communication, monitoring of assent and distress, and continued access during daily routines. The design does not isolate the doll as a stand-alone object from the additional attention, structured interaction, and relational support that accompany implementation.

Intervention deliverers must be registered nurses or certified nursing assistants with at least 6 months of dementia-care experience. All deliverers will complete an 8-h face-to-face study-specific training program covering attachment theory and person-centered care principles, the standardized activity sequence, communication skills and dignity-preserving language, assent and dissent monitoring, recognition of distress and over-attachment, safety monitoring and adverse-event documentation, infection-control procedures, and escalation routes. After training, each deliverer must pass a standardized role-play competency assessment scored by the research team against a structured checklist; deliverers who do not pass will repeat the relevant training modules before contributing to the trial.

During the introduction phase, trained deliverers will facilitate familiarization and support caregiving behaviors in a calm, familiar environment. The structured intervention comprises eight planned sessions delivered across approximately 15 days, scheduled on days 1, 3, 5, 7, 9, 11, 13, and 15. Each session is planned to last 20–30 min, adjusted to the resident’s attention, fatigue, and emotional response. The same core activity sequence will be used across intervention homes: introductory interaction with the doll, naming the doll, holding and bonding, reminiscence-oriented conversation, dressing and grooming, storytelling, music-based interaction, and shared closure activities. Sessions will be delivered individually whenever possible; small-group delivery is permitted only when consistent with the resident’s preference and the facility’s routine, and the format of every session (individual or small group) will be recorded as a process variable. After the structured phase, participants will continue to have access to the same doll within their daily routines until the 12-week follow-up.

The intervention is informed by attachment theory and person-centered care principles. It is intended to support emotional regulation, comfort, social engagement, and purposeful caregiving behavior rather than to compel any standardized response. Staff may gently invite interaction by offering the doll, asking open questions, or supporting preferred caregiving actions. Acceptable encouragement does not include insistence, repeated prompting after refusal, physical placement of the doll against the resident’s wishes, or staff statements that increase distress, guilt, or obligation.

Intervention fidelity will be monitored at three levels. First, every introductory session will be documented on a structured session checklist covering activity-sequence adherence, communication style, assent and dissent handling, and any adaptations. Second, an independent observer not involved in delivery will directly observe at least 20% of all introductory sessions at each intervention site, sampled across deliverers and across early, mid, and late phases of the introductory schedule, and will rate fidelity on the same structured checklist; inter-rater agreement between deliverers and observers will be summarized as percent agreement and Cohen’s kappa, and any systematic departure from the activity sequence will trigger a fidelity-recovery meeting. Third, follow-up access to the doll during routine care will be documented using routine activity logs and caregiver notes.

Participant engagement with the doll will be recorded as a structured process measure. Trained staff will document physical interaction, verbal interaction, caregiving behavior, duration of use, emotional response, refusal, distress, possessiveness, and any interruption or adaptation. To support reliability of engagement ratings, the research team will conduct an inter-rater agreement exercise (paired observations of at least five sessions per site) during deliverer training and again midway through the trial. These data will be used to describe intervention exposure and to support exploratory interpretation of heterogeneity in response. The activity-log template is provided as Supplementary File 1.

The structured doll-therapy activities and their conceptual basis are summarized in Table 1.

**Table 1 tab1:** Structured doll-therapy activities, planned timing, fidelity focus, and conceptual basis.

Session/planned day	Activity name	Core activity and fidelity focus	Conceptual basis
1/Day 1	Nice to Meet You	Introduce participants, staff, and caregivers; explain that the doll is an optional comfort and activity object; document assent, refusal, and baseline response.	Activity-based social engagement; person-centered introduction
2/Day 3	Thank You for Staying with Me	Introduce each participant’s individual doll; invite naming or familiarization without pressure; record acceptance and affective response.	Attachment theory; identity and belonging
3/Day 5	Love Me and Hug Me	Invite holding, touching, or comforting the doll according to preference; stop if refusal, fear, or agitation occurs.	Attachment theory; emotional regulation
4/Day 7	Listen to Me	Use open conversation or reminiscence prompts related to caregiving, family, or daily life; avoid corrective or deceptive language.	Attachment theory; reminiscence and self-identity
5/Day 9	Lovely Family	Support simple doll-care activities such as dressing or grooming; observe fine motor engagement and distress signals.	Attachment theory; purposeful activity
6/Day 11	Enjoying the Moment	Use music, storytelling, or calm shared activity with the doll; document duration and quality of interaction.	Attachment theory; positive affect and engagement
7/Day 13	Raising Babies	Simulate nurturing tasks only when welcomed by the resident; monitor possessiveness, conflict, or interference with care.	Attachment theory; caregiving role continuity
8/Day 15	Better Tomorrow	Review preferred activities, consolidate comfort routines, and plan safe continued access during routine care.	Attachment theory; continuity and closure

Sessions are scheduled on days 1, 3, 5, 7, 9, 11, 13, and 15. Each session lasts approximately 20–30 min and is adjusted to the resident’s attention, fatigue, and emotional response. Deviations from the planned schedule due to acute illness, fatigue, or staffing constraints will be documented.

The comparator is routine nursing care alone. Routine care may include assistance with eating, bathing, dressing, mobility, toileting, medication administration, health monitoring, social and recreational activities, psychological support, and communication with family members according to each facility’s usual practice. Control homes will not receive study-provided dolls, doll-therapy training, or the structured doll-therapy activity protocol during the study period. Other routine non-pharmacological activities, medication reviews, family visits, and clinical care will not be restricted because the trial is pragmatic, but major co-interventions and changes in routine care will be documented where feasible. Between-site variation in usual care will be described as contextual information and considered when interpreting the results. Because no active attention-control condition is included, observed differences will be interpreted as effects of the structured, staff-mediated doll-therapy care package, including doll use, staff training, structured interaction, relational engagement, and routine-care implementation, rather than as isolated doll-specific therapeutic effects.

### Safety monitoring and harms

Doll therapy is considered a low-risk psychosocial intervention, but potential adverse responses include distress, agitation, possessiveness, interpersonal conflict, family concern, worsening confusion, or over-attachment to the doll. Each participant in the intervention arm will be assigned an individual doll, and dolls will not be shared between residents. Dolls will be cleaned according to each facility’s infection-control procedures while preserving participants’ sense of ownership and comfort.

Resident assent will be monitored throughout the study. Refusal or dissent may be verbal, such as saying no or asking staff to remove the doll, or non-verbal, such as pushing the doll away, turning away repeatedly, crying, showing fear, increased agitation, or clear discomfort. If a resident shows refusal or distress, staff will stop the interaction for that occasion, remove or set aside the doll respectfully, provide reassurance, and record the event. Reintroduction may be attempted only when the resident is calm and willing. Two consecutive sessions with refusal or significant distress will trigger an individualized review by the site clinician; three consecutive refusals or any persistent doll-related distress will result in discontinuation of doll exposure for that participant, with the resident retained in the intention-to-treat analysis.

Adverse events will be graded as mild (transient distress resolving within the session), moderate (distress persisting beyond the session but resolving within 24 h, or non-injurious behavioral escalation), or severe (sustained distress beyond 48 h, hospitalization, injury, suspected harm to self or others, or death). All adverse events will be documented within 24 h by the site coordinator and reviewed by the principal investigator. Severe events and any unanticipated adverse events will additionally be reported to the institutional review board within 24 h of identification. Signs of persistent over-attachment, such as marked distress when separated from the doll, conflict with other residents, or interference with eating, sleep, hygiene, or clinical care, will trigger individualized review and adaptation. Safeguards to preserve dignity and autonomy include voluntary participation, proxy consent plus ongoing assent, non-deceptive introduction to families and staff, individualized stopping rules, private or respectful session settings, avoidance of infantilizing language, and documentation of adverse emotional or social reactions. Because this is a minimal-risk behavioral intervention with structured stopping rules and adverse-event review, no independent data monitoring committee is planned; this decision will be revisited if the adverse-event rate exceeds prior expectations.

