### Outcomes

Outcomes are organized into a transparent hierarchy that distinguishes (i) the outcome registered in ClinicalTrials.gov, (ii) the outcome given interpretive primacy for proximal clinical response, (iii) secondary clinical outcomes, and (iv) exploratory contextual outcomes and process measures. This structure is intended to clarify what the trial can describe as feasibility-oriented, preliminary, or contextual evidence, and how each outcome should be weighted in interpretation given the exploratory pilot design. Overall conclusions will be weighted first toward feasibility, acceptability, fidelity, safety, and implementation signals; second toward NPI-12 as the validated proximal behavioral outcome; and only cautiously toward medication outcomes as indirect medication-stewardship signals.

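### The mild grade and the distress part of the moderate grade are defined by a doll session, so the same transient distress has no grade in control homes or after about day 15 in intervention homes

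*Protocol article*

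**What the plan says.** Under Safety monitoring and harms the protocol article sets three grades:

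- Mild, and the start of moderate: "Adverse events will be graded as mild (transient distress resolving within the session), moderate (distress persisting beyond the session but resolving within 24 h".
- Moderate in full: "moderate (distress persisting beyond the session but resolving within 24 h, or non-injurious behavioral escalation".
- Severe: "severe (sustained distress beyond 48 h, hospitalization, injury, suspected harm to self or others, or death".

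The same section makes recording general: "All adverse events will be documented within 24 h by the site coordinator and reviewed by the principal investigator". Setting, participants, and recruitment has every participating home appoint a site coordinator. Data management lists adverse responses among the data that trained personnel record at each home on standardized forms.

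Under Intervention and comparator, the eight introductory sessions fall on days 1 to 15, and residents keep the doll in daily routines until the 12-week follow-up. The deliverers' 8-hour course includes "safety monitoring and adverse-event documentation". For the comparator: "Control homes will not receive study-provided dolls, doll-therapy training, or the structured doll-therapy activity protocol during the study period".

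The Outcomes section gives safety its weight: "Overall conclusions will be weighted first toward feasibility, acceptability, fidelity, safety, and implementation signals".

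**The concern.** A severity scale should give the same grade to the same event wherever and whenever it occurs. Here the two lower distress categories depend on the end of a session. A control resident who is distressed for ten minutes has no session against which to judge the episode. Nor has an intervention resident distressed during ordinary doll use in week 8.

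The text does not confine event recording to the intervention arm, so data will come from all six homes. The lower part of the scale, however, fits only one arm, and only for its first two weeks or so. A table of events by grade and arm would then reflect where the definition can be applied and how closely residents are watched, as well as any effect of the package. This matters because safety ranks ahead of NPI-12 in the stated weighting, the Discussion makes its favorable message depend partly on the package proving safe, and the decision to have no independent monitoring committee is to be revisited if the adverse-event rate is higher than expected.

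**Working it through.** The document gives no adverse-event rate, safety sample size or safety precision, so there is no figure to reproduce. The check is mainly textual.

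**1. Which criteria need a session?**

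| Grade | Criterion | Needs a session? | Usable in control homes? |
|---|---|---|---|
| Mild | Transient distress | Yes | No |
| Moderate | Distress lasting past the session, gone by 24 h | Yes | No |
| Moderate | Non-injurious behavioral escalation | No | Yes |
| Severe | Distress beyond 48 h, hospitalization, injury, suspected harm, death | No | Yes |

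Two of the criteria fail in control homes. The others do not.

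**2. How long does the session reference exist in the intervention arm?** Inputs: last session on day 15; follow-up of 12 weeks (Intervention and comparator; Study design).

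- Follow-up: 12 x 7 = 84 days.
- Days after the last session: 84 - 15 = 69, and 69/84 = 82%.
- This assumes that the 12 weeks start with session 1. If session 1 comes d days later, the share of the remaining time is (69 - d)/(84 - d). With d = 28 (an assumption), it is 41/56 = 73%.
- Scheduled session time per resident: 8 x 20 = 160 to 8 x 30 = 240 minutes in total.

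**3. Is observation the same in both arms?** At target recruitment there are 142/2 = 71 residents per arm, so at most 71 x 8 = 568 planned sessions, each with a structured checklist. Refusals and discontinuations lower this number. No corresponding observed occasion is described for control homes. Training that names event documentation is described for deliverers; the content of the training given to recording staff in control homes is not described.

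**4. Do the limits meet?** The distress part of moderate stops at 24 h, and the distress part of severe starts beyond 48 h. Distress that resolves at, say, 36 h without behavioral escalation or another severe criterion meets neither definition. This gap affects both arms.

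**5. Illustration only; none of these rates is in the document.** Suppose the true risk of lower-grade distress is equal in both arms, capture is complete in intervention homes, and control homes capture a fraction s of that. The apparent risk ratio is 1/s: 1/0.25 = 4.0, 1/0.50 = 2.0, 1/0.75 = 1.33. At an assumed true risk of 20%, the intervention arm would record 71 x 0.20 = 14.2 residents with events. Control would record 14.2 x 0.25 = 3.6, 14.2 x 0.50 = 7.1 or 14.2 x 0.75 = 10.7. This shows the direction of the distortion and does not predict its size.

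**The case against.** The best defense is that the grades are a tolerability scale for residents exposed to the doll. No section announces a between-arm comparison of adverse events, and the Discussion promises only safety observations. Fidelity and acceptability, listed beside safety in the first rank, are studied only in intervention homes. The harms named at the start of the safety section are largely responses to the doll. A common form and a coordinator briefing are also details that an article often leaves to fuller documents.

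Much of this stands. It does not remove the problem, for two reasons. The text requires all adverse events to be documented by coordinators, who exist in every home, and nowhere limits grading to the intervention arm. And a tolerability scale for exposed residents would still lack a reference point after day 15, when exposure continues. The definition is stated in the article, so this is a rule that does not work as written, not an omitted detail.

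A reader might also infer more than the text supports:

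- *That every grade depends on a session.* Behavioral escalation and all severe criteria do not.
- *That only intervention staff are trained to record events.* Data management places trained personnel in each home. What can be said is that training naming event documentation is described only for deliverers.
- *That severe events have no usable control rate.* Their definitions apply in both arms, coordinators give access to source documents in every home, and hospital transfers in the medication assessment windows are to be recorded, where available, without restriction by arm. Including events of any cause in a severity grade is not a fault either, since severity and causality are separate judgments.
- *That the doll arm must show a particular excess of mild events.* Any such count needs a distress rate and a control capture rate that the document does not give.

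**Conclusion.** The point holds for the mild grade and for the distress part of the moderate grade. As written, these cannot be applied in control homes, or for about 82% of intervention follow-up counted from the first session. Counts in these grades should not be read between arms. The conclusion rests on the wording and on reading the session as a doll-therapy session, the only kind that the article schedules.

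It does not extend to a claim that safety as a whole cannot be compared. Hospitalization, injury, death, distress beyond 48 h and behavioral escalation are comparable in definition, provided that capture is the same in all homes. The article plans no between-arm safety test that this would invalidate; the risk lies in how a first-ranked conclusion would be tabulated and read. The distortion cannot be sized from the document.

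Separately, the gap between 24 h and 48 h is an internal inconsistency whichever arm is considered. The wording should be corrected before events are graded.

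**What to change.** 1. In Safety monitoring and harms, define mild distress and the distress part of moderate without reference to a session, so that they apply in both arms throughout the 12 weeks.
2. In the same edit, reconcile the 24 h and 48 h limits so that every duration of distress falls in one grade. Which grade is for the investigators to decide.
3. Capture arm-neutral events (hospitalization, injury, death, behavioral escalation, sustained distress) on one form, from the same kinds of record, in all six homes. Report them by arm and by home.
4. Report session- and doll-related responses (refusal, distress during doll use, possessiveness, over-attachment) separately as intervention-arm tolerability, and state that they are not compared with control.
5. Give the coordinators of the three control homes the event-documentation part of the training, without doll content.

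The cost is a change of wording, one common form, slightly more form work in control homes and a short briefing there. Randomization, sample size and the efficacy analyses are unaffected.

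### The adverse-event severity grades leave distress that resolves after 24 h and by 48 h without a grade

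*Protocol article*

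**What the plan says.** The protocol article, under safety monitoring and harms, prints a three-level severity scale:

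- "mild (transient distress resolving within the session")
- "moderate (distress persisting beyond the session but resolving within 24 h, or non-injurious behavioral escalation")
- "severe (sustained distress beyond 48 h, hospitalization, injury, suspected harm to self or others, or death")

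In the article the two upper grades follow directly on one another, with nothing between their time limits: "moderate (distress persisting beyond the session but resolving within 24 h, or non-injurious behavioral escalation), or severe (sustained distress beyond 48 h".

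Two procedures follow in the same section. One applies whatever the grade: "All adverse events will be documented within 24 h by the site coordinator and reviewed by the principal investigator". The other depends partly on the grade: "Severe events and any unanticipated adverse events will additionally be reported to the institutional review board within 24 h of identification".

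The same section lists distress first among the potential adverse responses to the doll. It also contains a stopping rule under which persistent doll-related distress ends exposure to the doll for that resident. That rule uses no severity grade and states no duration.

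The outcomes section sets the weight that safety will carry: "Overall conclusions will be weighted first toward feasibility, acceptability, fidelity, safety, and implementation signals". The NPI-12 comes second, and medication outcomes are to be read only cautiously.

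**The concern.** A severity scale should give every event exactly one grade. This one is defined by explicit time limits, and the limits of the two upper grades do not meet. Distress is the first harm that the section names, so the gap lies on the axis along which doll-related events are most naturally graded.

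This is not detail that a condensed article has left to a fuller document. The article states the whole scale with its cut-offs, and followed as written the scale fails for one class of event.

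At stake is the table of adverse events by severity. If a resident in one of the three intervention homes is distressed for a day and a half, one home could round the event down to moderate, another up to severe, and a third could leave the grade blank. Each choice could be defended from the text. Pooled counts by grade would then partly reflect local convention, in a trial that draws its first conclusions from safety among other feasibility outputs.

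**Working it through.** No sample-size, power or error-rate figure bears on this point, and the plan gives no figure to reproduce. The check is whether the definitions cover the whole duration scale.

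**Inputs**, all from the safety monitoring and harms section of the protocol article. Let T be the time until distress resolves, and S the end of the session.

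- Mild: T ≤ S.
- Moderate, duration criterion: S < T ≤ 24 h.
- Moderate, other criterion: non-injurious behavioral escalation, with no time limit.
- Severe, duration criterion: T > 48 h.
- Severe, other criteria: hospitalization, injury, suspected harm to self or others, or death, with no time limit.

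**Step 1: coverage by duration.** The union of the three duration criteria is T ≤ 24 h together with T > 48 h. The uncovered part is 24 h < T ≤ 48 h, with width 48 − 24 = 24 hours.

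**Step 2: worked cases, distress as the only feature.**

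| Time to resolution | Mild | Moderate | Severe | Grade |
|---|---|---|---|---|
| Within the session | yes | no | no | mild |
| 10 h | no | yes | no | moderate |
| 24 h | no | yes | no | moderate |
| 30 h | no | no | no | none |
| 48 h | no | no | no | none |
| 50 h | no | no | yes | severe |

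**Step 3: can another criterion supply the grade?** Sometimes. Distress of 30 h with non-injurious escalation is moderate. Distress of 30 h with injury, hospitalization or suspected harm is severe. Only distress without any of these stays ungraded.

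**Step 4: does any other text close the gap?** No. The stopping rule speaks of persistent distress without a duration and assigns no grade. The separate provision on over-attachment triggers individual review, again without a grade. The remaining sections contain no severity definitions.

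**Step 5: which procedures depend on the missing grade?**

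- Documentation within 24 h and review by the principal investigator apply to all adverse events, so they are unaffected.
- The stopping rule does not use the grade, so it is unaffected.
- Expedited reporting to the review board applies to severe or unanticipated events. Distress of 30 h does not meet the severe duration limit, and distress is a listed response. As written, it falls below the reporting threshold unless another severe criterion is met or the event is unanticipated in some other way.
- Assignment of a grade, and any tabulation by grade, has no rule for these events.

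**The case against.** The strongest reply is that little depends on the gap. Every event is recorded and reviewed whatever its grade, protection of the resident runs through rules that do not use the grade, and the lower limit of severe distress is explicit. The principal investigator reviews all adverse events and could apply one convention throughout. The trial is an exploratory pilot, and no efficacy estimate is touched.

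Most of this stands, and it limits the point to grading. It does not remove it: review by one person could make the grades consistent, but the convention would be unwritten and might be chosen after events had been seen.

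A reader might infer more than the document supports:

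- **That such events would be left out.** The requirement to document applies to all adverse events.
- **That the gap makes expedited board reporting arbitrary.** The severe limit for distress is stated, and the gap lies below it. A home that rounds up would report more than the text requires, but the threshold itself does not move.
- **That the oversight trigger cannot work.** On the decision to have no data monitoring committee, the article says "this decision will be revisited if the adverse-event rate exceeds prior expectations" and gives no expected rate. A condensed article commonly leaves such a figure to the full protocol, which is not shown, so its absence here is not a finding.
- **That grades cannot be compared between arms because control homes hold no doll sessions.** The article plans no such comparison. It frames these harms as responses to the doll.
- **That multiplying residents by planned sessions gives the scale of the problem.** That product counts planned contacts and says nothing about how many events last between 24 and 48 h.

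**Conclusion.** The point holds in a narrow form. The printed severity scale is not exhaustive: distress alone that resolves after 24 h and by 48 h has no grade, a band of 24 hours. The likely consequence is inconsistent grading between homes and a less reliable severity table in an output that the trial places in its first tier. Participant protection, documentation, the stopping rule, the severe-event reporting threshold and the efficacy estimates are not shown to be affected.

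The conclusion rests on two assumptions: that both time limits are counted from the same starting point, and that the wording is applied literally. The number of affected events is unknown. It could be none, and the article offers no basis for an estimate. This is a drafting defect in a stated rule, modest in effect and worth correcting because the correction is simple.

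**What to change.** Before the first session, the clinical team and the review board should reconcile the moderate and severe definitions so that every duration of distress falls in exactly one grade. Where the boundary lies is a clinical decision for them, and none is suggested here. The adverse-event form and the severity-grading part of staff training should then carry the agreed wording, so that all homes grade from the same text.

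The cost is a short protocol amendment, notification of the sites and the ethics committee (which the article already foresees for important amendments) and a small change to one form. Sample size, schedule and analysis are unchanged. If sessions have already begun, the agreed definition can be applied to events on record where the time to resolution was noted, and the date of the change should be reported.
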